## 1.3. Recommended Schedule of Activities

Visit schedules for the group of SMA patients treated with DMT (including nusinersen and other DMTs) and the group of untreated patients will be described in Table 1. Data for the registry will only be collected within regular SMA patient visits.

CONFIDENTIAL

The information contained herein may not be used, disclosed, or published without the written consent of  
Biogen

Table 1. Expected Tests and Assessments

| Tests and Assessments                                            | Enrollment data collection points | Follow-up data collection points
For nusinersen-treated patients, it is expected they will be observed on days 14, 28, and 63 and every 4 months thereafter.
For untreated patients or those on other DMTs, it is expected they will be observed on days 90a and 180 and every 6 months thereafter. |
|------------------------------------------------------------------|-----------------------------------|------------------------------------------------------------------------------------------------------------------------------------------------------------------------------------------------------------------------------------------------------------------------------------------------------------------------------------|
|                                                                  | V0                                | V1-V17                                                                                                                                                                                                                                                                                                                             |
| Informed Consent                                                 | X                                 |                                                                                                                                                                                                                                                                                                                                    |
| Review of eligibility criteria                                   | X                                 |                                                                                                                                                                                                                                                                                                                                    |
| Demographics                                                     | X                                 |                                                                                                                                                                                                                                                                                                                                    |
| Living status                                                    | X                                 | X                                                                                                                                                                                                                                                                                                                                  |
| Genetic diagnosis                                                | X                                 |                                                                                                                                                                                                                                                                                                                                    |
| Clinical observations                                            | X                                 | X                                                                                                                                                                                                                                                                                                                                  |
| Scoliosis                                                        | X                                 | X                                                                                                                                                                                                                                                                                                                                  |
| Motor function                                                   | X                                 | X                                                                                                                                                                                                                                                                                                                                  |
| Wheelchair use b                                      | X                                 | X                                                                                                                                                                                                                                                                                                                                  |
| Nutrition                                                        | X                                 | X                                                                                                                                                                                                                                                                                                                                  |
| Pulmonary function c                                  | X                                 | X                                                                                                                                                                                                                                                                                                                                  |
| Therapies and medications (including DMTs other than nusinersen) | X                                 | X                                                                                                                                                                                                                                                                                                                                  |
| Hospitalizations and comorbidities                               | X                                 | X                                                                                                                                                                                                                                                                                                                                  |
| Clinical research                                                | X                                 | X                                                                                                                                                                                                                                                                                                                                  |
| Motor measures                                                   | X                                 | X                                                                                                                                                                                                                                                                                                                                  |
| Patient reported outcomes                                        | X                                 | X                                                                                                                                                                                                                                                                                                                                  |
| Electrophysiology and biomarkers                                 | X                                 | X                                                                                                                                                                                                                                                                                                                                  |
| Nusinersen/other DMT treatment utilization d          | X                                 | X                                                                                                                                                                                                                                                                                                                                  |
| Adverse events / Serious adverse events                          | X                                 | X                                                                                                                                                                                                                                                                                                                                  |
| End of data collection                                           |                                   | X                                                                                                                                                                                                                                                                                                                                  |

**X:** based on the patient's routine clinical visit, time points the study visits will most likely happen. No extra study visits, examinations, laboratory tests or procedures will be mandated

a. In children with SMA type 1 < 2 years of age

b. For patients ≥ 2 years old

CONFIDENTIAL

- c. If the patient is sufficiently cooperative due to age
- d. For patients treated with nusinersen or other DMTs

CONFIDENTIAL

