| Additional Objectives                                                                                | Additional Endpoints                                                                                                                                                                                                                    |
| To describe the effectiveness of DMT.                                                                | Time to mortality, motor function, motor measures, pulmonary function, scoliosis, hospitalizations and comorbidities, clinical observations, patient reported outcomes, wheelchair use, nutrition and electrophysiology and biomarkers. |
| To evaluate the safety of DMT.                                                                       | Adverse events and serious adverse events.                                                                                                                                                                                              |

CONFIDENTIAL

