## **8. WITHDRAWAL OF PATIENTS FROM THE STUDY**

The registry patient can have his/her participation in the registry terminated prematurely at any time, without having to give reasons. Patients must be withdrawn from the study for any one of the following reasons:

- The participant withdraws consent.
- The participant is unwilling or unable to comply with the protocol.
- The physician withdraws the participant from the study for medical reasons.

The treating physician has the right to terminate registry participation of a patient according to the following conditions:

- Loss of contact.
- Logistical reasons (patient changes his/her doctor or hospital or moves to another location).
- Extreme circumstances arise which make any registry-relevant follow-up impossible.

The reason for the participant's withdrawal from the study must be recorded in the participant's case report form (CRF).

The investigator has the right to terminate the registry at one of the centers. The registry can be terminated prematurely at his center by the investigator if, for instance, unforeseeable circumstances have arisen at the trial center which preclude the continuation of the registry or the investigator considers that the resources for continuation are no longer available. The sponsor can initiate the exclusion of a center from further participation if, serious problems arise with regard to the quality of the collected data which cannot be resolved. Premature termination at one of the trial centers does not automatically mean a termination of the registry for already enrolled registry patients. The documentation of already enrolled registry patients will be reviewed for completeness and plausibility. Queries may be raised for further clarification before the center is closed. These queries must be answered properly by the center.

The sponsor/coordinating investigator is under obligation to monitor the progress of the registry about intended developments and, if necessary, initiate the termination of the entire registry. The sponsor/coordinating investigator will be supported in this responsibility by the contract research organization, if necessary. Further, the coordinating investigator can prematurely terminate the registry if sufficient financial funding is not available anymore. All published data will be stored and archived for 10 years.

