### **8.1. Lost to Follow-Up**

Patients will be considered lost to follow-up if they repeatedly fail to return for routine clinic visits and are unable to be contacted by the study site. Contact attempts should be documented in the participant's medical record. Should the participant continue to be unreachable, that participant will be considered to have withdrawn from the study with a primary reason of lost to follow-up.

Reasons for loss to follow-up should be documented by the physician in charge in the respective section of the CRF. Specific recommendations for the respective follow-up visits of patients to evaluate other treatments or interventions will be added to the schedule of activities.

CONFIDENTIAL

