This registry study will include both retrospective and prospective data collection. Eligible SMA patients will be recruited during the 24-month recruitment period and will be prospectively followed up to the end of study or deaths or willing to drop out, whichever comes first. If patients received DMT (including nusinersen and other DMTs) prior to the recruitment initiation and post April 28th, 2019 (as the date the first DMT, nusinersen, was launched in Chinese market), data will be retrospectively collected via medical chart review. Retrospective data collection will be considered complete for a participating patient if data of last available medical chart or latest survival status before recruitment initiation have been recorded in the electronic case report form (eCRF). Otherwise, patients will be prospectively followed up to the end of study or deaths or willing to drop-out, whichever comes first, after signing the ICF. For the DMTs treated group, the date of patients initiating DMT will be defined as the index date. For patients not receiving DMTs, the date of enrollment into the registry will be the index date. Baseline data will be collected within 30 days prior to the index date. Diagram of data collection is provided in Figure 1.

Since this is a non-interventional study and does not impose a visit schedule, patients will be treated according to physician's decisions. Only data that are available during routine visits will be documented. Recommended data collection schedules are set up to reflect the most likely patterns of routine clinical care of patients with and without DMT. To ensure the excellent level of compliance on data collection, schedule points are set to follow clinical routine visits, most likely happen on day 0, 14, 28, 63 then every 4 months for patients treated with nusinersen, and at day 0, 90 (in children with SMA type 1 < 2 years of age), 180 then every 6 months for untreated patients or those on other DMT. Retrospective data will be extracted according to the schedule as well.

CONFIDENTIAL

All data collected within the registry will be entered to the registry-specific e-forms by the responsible investigator, or a designated person, as timely as possible. Data entry and data corrections on e-forms are automatically tracked in the audit trail created by the EDC system. The EDC system and related IT infrastructure of this project will be based inside China.

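### Survival could be overstated: registry data are tied to routine visits, and no vital-status check is described for children who withdraw, move away or cannot be reached

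*Protocol*

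**What the plan says.** Time to mortality is an additional endpoint in Section 4, under the effectiveness of disease-modifying therapy (DMT); the list there begins "Time to mortality, motor function, motor measures, pulmonary function". Section 9 also names living status among the data for natural history, which is part of the primary objective. Section 11.3 plans Kaplan-Meier estimates for time-to-event endpoints.

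Table 1 in Section 1.3 marks "Living status" at enrollment and across V1-V17. Two statements confine collection to visits: "Data for the registry will only be collected within regular SMA patient visits" in Section 1.3 and "Only data that are available during routine visits will be documented" in Section 9.

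On exits, Section 8.1 covers children who repeatedly miss visits and cannot be contacted: "Should the participant continue to be unreachable, that participant will be considered to have withdrawn from the study". Section 8 gives the treating physician the right to end participation on several grounds, one of them being "Logistical reasons (patient changes his/her doctor or hospital or moves to another location".

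Deaths also have a route through safety reporting. Section 10.3.2 puts any SAE between consent and completion or withdrawal on the case report form (CRF), whatever its relation to DMT. Section 10.3.2.1 asks for fatal events to be reported within 24 hours once the site knows of them, and for death certificates to be sought.

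**The concern.** A child who has died attends no further visit, so a visit-based item cannot record the event that defines the endpoint. If the site does not hear of the death, the rules in Sections 8 and 8.1 close the child as lost or moved. The death then enters the Kaplan-Meier analysis as censoring. Such censoring is informative, and it can only push the survival curve upward.

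The gap lies in data collection, so an analysis plan cannot repair it: no censoring rule recovers a death that was never recorded. Natural-history survival looks most exposed, because the safety route that would otherwise catch deaths is least clear for untreated children.

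**Working it through.** **1. The schedule, as a check on the plan's own figure.** For nusinersen: "For nusinersen-treated patients, it is expected they will be observed on days 14, 28, and 63 and every 4 months thereafter". Day 63 is about month 2.07. Fourteen further 4-month steps reach 2.07 + 14 × 4 = 58.07 months, inside the 60-month limit in Section 5.2. That gives 3 + 14 = 17 follow-up visits, which matches V1-V17. On the schedule for untreated children and those on other DMTs (day 90 for type 1 under 2 years, day 180, then every 6 months), the count is 11, or 10 without day 90. Table 1 is internally consistent, and living status is tied to these visits.

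**2. Which deaths have a required route into the data.**

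| Situation | Route in the protocol |
|---|---|
| Treated child dies before withdrawal, site learns of it | SAE on the CRF (10.3.2, 10.3.2.1) |
| Child dies, family unreachable, site never learns | None; closed as lost to follow-up (8.1) |
| Child dies after being closed as moved or lost | SAE form only if considered related to nusinersen (10.3.2) |
| Untreated child dies | Unclear: Section 10.1.2 defines SAEs for patients given a pharmaceutical product, and Section 9 collects safety data among patients on treatment |

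For retrospective data, Section 9 names the latest survival status as one way for collection to be complete. The prospective phase has no counterpart.

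**3. Size, under assumptions.** The protocol gives no mortality rate, loss rate or share of missed deaths. Let S be true survival, and let a share f of deaths at every time be censored instead of counted. The recorded hazard is then (1 − f) times the true hazard, and the Kaplan-Meier estimate tends to S^(1−f).

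With true mortality of 50% (S = 0.50), mortality reads as 1 − 0.5^(1−f):

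- f = 10%: 1 − 0.5^0.90 = 46.4%
- f = 25%: 1 − 0.5^0.75 = 40.5%
- f = 50%: 1 − 0.5^0.50 = 29.3%

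Across a wider range of assumed true survival at 60 months, the displayed survival would be:

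| True S | f = 10% | f = 25% | f = 50% |
|---|---|---|---|
| 95% | 95.5% | 96.2% | 97.5% |
| 90% | 91.0% | 92.4% | 94.9% |
| 80% | 81.8% | 84.6% | 89.4% |
| 50% | 53.6% | 59.5% | 70.7% |

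The formula places censoring at the time of death; in practice it would fall at the last visit. A simulation with 600 patients, exponential deaths and censoring at the last of 4-monthly or 6-monthly visits was run for true survival of 90%, 80% and 50%. It agreed with the formula to within 0.5 percentage points. The upward bias over the table runs from about 0.5 to 21 points, and is zero if no death is missed.

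**The case against.** The strongest reply is that deaths do not depend on visits at all. SAE recording starts at consent and is triggered by awareness. Section 10 has families given site telephone numbers for reporting adverse events and emergencies, and Section 10.7.1 has investigators actively pursue SAE follow-up. Section 8.1 requires failed contact as well as missed visits, and a family that is reached can report a death. Closing a child who moves is a right of the physician, not a duty. Table 1 has an end-of-data-collection row whose fields are not shown.

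All of that stands. A reader might infer that mortality rests solely on the visit item, or that every death between visits is lost. The documents do not support either reading: a death in a treated child that the site hears of before withdrawal should be captured. Nor do they support saying that every relocated child is closed.

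The reply does not close the gap. Awareness is the condition that fails for the child who cannot be reached. Section 10.3.2.1 could be read as covering any death the site later learns of, but it sits under a section whose CRF recording period stops at completion or withdrawal. Section 8.1 asks for contact attempts to be documented, not for vital status to be established.

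A difference in bias between groups because of 4-monthly versus 6-monthly visits is possible but not established. Type 1 children under 2 also have a day-90 visit, and children on other DMTs share the untreated schedule.

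**Conclusion.** The point holds as a conditional risk. Followed as written, the rules can turn unseen deaths into censoring, which would overstate survival. The visit-only statements in Sections 1.3 and 9 also conflict in wording with the awareness-based reporting in Sections 10.3.2 and 10.3.2.1.

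The size is unknown. A reader might take the 46%, 41% and 29% as estimates, or conclude that survival will be overstated. Neither follows, since both the 50% mortality and the values of f are assumptions. Table 2 gives a natural life expectancy under 2 years for type 1, but that is not survival from enrollment, which is the index date for untreated children.

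Time to mortality is one of many additional endpoints, and Section 4 gives primary endpoints as not applicable. The issue merits correction because the remedy is cheap and the missing information may be hard to recover later. The absence of a censoring rule is no part of this finding; it can properly sit in the statistical analysis plan.

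**What to change.** - In Sections 1.3 and 9, exempt vital status from the visit-only rule, and reconcile that rule with Section 10.3.2.
- State that deaths of all enrolled children, treated or untreated, are recorded on the CRF.
- Record alive or dead, the date and the source of information during the contact attempts that Section 8.1 already calls for, and at withdrawal, relocation or loss to follow-up.
- Repeat this before each yearly data cut (Section 11.4 already plans yearly interim analyses) and at the end of data collection, unless consent for contact was withdrawn.

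The cost is amendment wording, one set of CRF fields, a small amount of site effort for children out of contact, and consent wording that allows continued vital-status contact. The survival censoring rule can be left to the statistical analysis plan.
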